## Abstract

**Background:**

Heart failure (HF) remains a disease of notable disparity for rural veterans, despite recent advancements in clinical treatment. Managing HF in the home is stressful and complex for rural veterans who experience unique barriers to optimal physical and mental health, necessitating adequate support and problem-solving skills.

**Objective:**

This study aims to (1) adapt, to the rural sociocultural context, a culturally sensitive, tailored, telephone support and problem-solving intervention (CARE-HF [Supporting Physical and Mental Health in Rural Veterans With Heart Failure]) using findings from preliminary qualitative research and (2) evaluate the effects of CARE-HF on problem-solving and physical and mental health outcomes among rural veterans with HF.

**Methods:**

This study involves a repeated-measures, single-group design. The intervention content was adapted and tailored to the rural sociocultural context using preliminary qualitative data and guided by the Theories of Social Problem-Solving and Stress, Appraisal, and Coping. Veterans are recruited from Veterans Administration home-based cardiac rehabilitation clinics, cardiology clinics that serve veterans, veterans-based community resource centers, and social media campaigns. Veterans with HF (N=100) receive the CARE-HF intervention. This nurse-led intervention comprises 8 telephone sessions that use a five-step, problem-solving process to manage common HF problems in the home: (1) identifying the problem and viewing it in a positive manner, (2) goal setting, (3) generating potential strategies for problem management, (4) choosing and implementing strategies to manage the problem, and (5) evaluating strategy effectiveness. Veterans receive initial problem-solving training during the first session, with follow-up sessions focusing on problem-solving skill reinforcement and assisting veterans in applying these principles to manage self-identified, HF-related problems experienced in the home. Data are collected at baseline and 3, 6, 12, and 18 months from baseline on problem-solving and outcomes of interest (ie, HF self-care; HF symptoms; health care utilization; depressive symptoms; anxiety; HF-specific, health-related quality of life; stress; resilience; and coping). Demographic data will be analyzed using descriptive statistics and multilevel growth curve modeling with restricted maximum likelihood estimation to compare a series of models using Akaike information criteria and Bayesian information criteria fit indices while controlling for covariates.

**Results:**

Recruitment started in April 2023. As of December 2024, we have enrolled 56 veterans. Recruitment is anticipated to end in June 2025, with data collection continuing until all enrolled veterans have completed the 18-month follow-up period.

**Conclusions:**

Adapting and testing a culturally sensitive, tailored, telephone intervention to aid support and problem-solving in the home has the potential to provide individualized care to rural veterans where they reside, thereby reducing travel burden while also increasing access to evidence-based care programs. If effective, telephone support and problem-solving interventions could be a low-cost, accessible method to improve physical and mental health in rural veterans with HF.

**Trial Registration:**

ClinicalTrials.gov NCT05839067; https://clinicaltrials.gov/study/NCT05839067

**International Registered Report Identifier (IRRID):**

DERR1-10.2196/63498

## Introduction

### Background

Heart failure (HF) is a chronic, progressive disease of notable disparity for rural veterans despite recent advancements in clinical treatments [1] and overall improvements in HF-related outcomes [2]. Incidence, hospitalization, and mortality rates continue to be highest in rural versus urban individuals with HF [2,3]. In rural veterans, specifically, HF is the second leading cause of cardiovascular-related hospitalization, accounting for about 30% of total hospitalizations [4]. Lower levels of health literacy, higher rates of food insecurity, the presence of food deserts, the lack of community support services, poverty, and limited health care access contribute to the disparities in HF-related outcomes in rural veterans [5-7] and influence physical and mental health [7].

Rurality impacts patients’ ability to maintain optimal HF self-care and disease management in the home. Specifically, rural veterans with HF experience unique challenges, which are stressful, such as difficulties in obtaining fresh fruits and vegetables and low-sodium foods, which are a vital component of the HF dietary regimen [8]. The lack of local health care services and pharmacies, as well as public transportation, adds to the complexity of managing HF in a rural area [8] and increases the travel burden for veterans associated with receiving medical care [9]. In fact, only 9% of physicians practice in rural areas, which is significant given that 20% of the population in the United States lives in rural areas [6]. These rural-related social determinants of health play a crucial role in the ability to maintain optimal HF self-management and influence patient outcomes in rural veterans with HF [7].

Likewise, depression and anxiety are influenced by the progression of HF [10], with increased symptoms and decreased physical functioning contributing to poor mental health [11,12], and are associated with higher mortality and hospitalization rates [10,13]. Notably, depression and suicide rates are highest in rural patients compared to their urban counterparts, yet only 10% of mental health professionals practice in rural areas, leaving many rural veterans without access to mental health care [14] and placing them at even greater risk for poor HF outcomes [10,13]. Thus, rural veterans living with HF lack substantial support in aiding disease management and mitigating the negative emotions that often accompany living with HF, necessitating the development of novel interventions to support physical and mental health in the home.

Social support and problem-solving are essential coping resources that aid stress management, support resiliency, and enhance coping processes [15,16]. In rural veterans with HF, social support and problem-solving skills are critical to maintaining physical and mental health [8,17,18]. Patients with HF need to appraise and manage diverse symptomatology, adhere to dietary restrictions, cope with negative emotions, and negotiate daily activities [11,12]. Rural veterans with HF also need to successfully address rural-related challenges and barriers that undermine overall health [7]. Previous research suggests that the use of rational, systematic problem-solving strategies to manage HF-related problems is associated with better HF self-care [8,17] and may reduce HF symptom severity [18] and mental distress [17]. However, rural veterans often lack access to support and problem-solving interventions in their communities. Furthermore, when such services are available, they typically are not tailored to the rural sociocultural and educational context, nor are they able to address the specific emotional needs of veterans [19].

Culturally sensitive, tailored interventions that provide support and focus on enhancing problem-solving skills [16] hold considerable promise for increasing uptake in rural veterans with HF. Tailored support and problem-solving programs may be beneficial for veterans who need more assistance outside of a “standardized, one-size-fits-all” disease self-management program. Furthermore, the use of telephones allows for an easy-to-access, cost-effective, and successful modality for delivering such interventional programs to rural areas where access to broadband internet may still be problematic [20-22].

Our previous research assessed the preliminary efficacy of a 12-week, nurse-led, tailored, telephone-based, problem-solving and support intervention (Coping in Heart Failure [COPE-HF] Partnership) for patients with HF on changes in self-care, HF symptoms, depressive symptoms, and health care utilization in a three-arm randomized clinical trial [17,18]. Participants in the COPE-HF Partnership were all recently discharged from an acute care facility for issues related to HF and resided primarily in urban areas. A trained nurse interventionist partnered with the patient to manage HF-related self-care and disease management problems encountered in the home. Data were collected at baseline and 5, 9, and 13 weeks. The intervention was associated with improvements in self-care management; notably, patients had less health care utilization over the intervention period versus the other groups [17]. Patients who received the intervention also reported fewer HF symptoms, with a significant decrease in HF symptom severity over the intervention period [18]. Although not significant, improvements in depression were also found in the intervention group [17].

To prepare for the sociocultural adaptation of the CARE-HF (Supporting Physical and Mental Health in Rural Veterans With Heart Failure) intervention to the rural population, we conducted a qualitative study with rural patient–care partner dyads living with HF (n=11) to identify and describe the problems experienced in the home related to HF and associated management strategies [8]. The findings of this study showed that rural residents with HF experience significant problems related to self-care and disease management adherence due to the rural environment and lack of resources, as well as differences in cultural and personal values and beliefs related to health care. These problems resulted in a variety of physical and mental health sequelae and strained interpersonal relationships. However, most dyads developed effective workarounds and management strategies to overcome these challenges [8]. The problems and management strategies identified in this study provide the basis for the adaptation of intervention content for the rural population included in the CARE-HF intervention.

The CARE-HF also builds upon the COPE-HF Partnership intervention, in that it includes self-care and disease management components [17,18]. However, it differs in that the CARE-HF intervention is more holistically focused, also incorporating mental health, interpersonal, and social components. In addition, all components of the CARE-HF intervention are adapted to the rural sociocultural context and include specific problems and management strategies pertaining to physical and mental health drawn from the rural setting [8]. Because of the expanded focus of the CARE-HF intervention, additional study outcomes, not examined in the parent intervention, are included in the CARE-HF study.

### Conceptual Framework

The Theories of Social Problem-Solving [16] and Stress, Appraisal, and Coping [15] provide the foundation for the CARE-HF intervention (Figure 1). Rural veterans with HF encounter a unique variety of problems that require cognitive appraisal and appropriate problem-solving to successfully cope with HF-related challenges. The two-fold cognitive appraisal process is influenced by individual characteristics and consists of primary appraisal (determination of the significance of the problem) and secondary appraisal (evaluation of available resources) [15]. Effective problem-solving requires a positive problem-orientation approach which elicits rational problem-solving versus avoidance, impulsivity, and carelessness. Problem-solving involves accurate problem identification, generation of appropriate strategies, active decision-making, and strategy implementation and evaluation [16]. The goal of the CARE-HF intervention is to move rural veterans with HF toward a positive problem orientation and use of rational problem-solving strategies, thereby supporting a more adaptive problem-solving style and enhancing physical and mental health [15,16].

**Figure 1 figure1:**
[figure not shown]
Conceptual model based on the Theories of Social Problem-Solving and Stress, Appraisal, and Coping.

### Purpose, Aims, and Hypotheses

The overall purpose of this study is to adapt to the rural sociocultural context and test the efficacy of a tailored, telephone-based intervention (CARE-HF) to support the physical and mental health of rural veterans by enhancing disease self-management and coping processes. To accomplish this goal, our research aims are to:

Adapt the CARE-HF intervention content to the rural sociocultural context using findings from preliminary qualitative research.Examine the effectiveness of the CARE-HF intervention on study outcomes (HF self-care, HF symptoms, health care utilization, depressive symptoms, anxiety, health-related quality of life, stress, resilience, and coping), process (problem-solving), and antecedent (social support) in a sample of rural veterans with HF (N=100) at baseline and 3, 6, 12, and 18 months from baseline.

Our hypotheses are as follows:

Hypothesis 2a: Increases in HF self-care, health-related quality of life, resilience, coping, and problem-solving will be noted at 3 months from baseline and sustained throughout the 18-month follow-up period.Hypothesis 2b: Decreases in HF symptoms (frequency, severity, and interference with physical activity and enjoyment of life), health care utilization, depressive symptoms, anxiety, and stress will be seen at 3 months from baseline and sustained throughout the 18-month follow-up period.

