### Data Collection

Telephone data collection is conducted by a trained research assistant who verbally asks each item and records participants’ responses in an online HIPAA (Health Insurance Portability and Accountability Act)–compliant Qualtrics database. Data are collected at baseline and 3, 6, 12, and 18 months from baseline. In addition to a sociodemographic and clinical survey (age, gender, comorbidities, education, and HF class), a set of self-report surveys is used to measure the study variables (Table 1). We also collect data on standard Veterans Administration Office of Rural Health metrics.

**Table 1 table1:** Study variables.

Variables		Baseline	3 months	6 months	12 months	18 months

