**Outcomes**						
	HF^a^ self-care	✓	✓	✓	✓	✓
	HF symptoms	✓	✓	✓	✓	✓
	Health care utilization		✓	✓	✓	✓
	Depressive symptoms	✓	✓	✓	✓	✓
	Anxiety	✓	✓	✓	✓	✓
	HF-specific, health-related quality of life	✓	✓	✓	✓	✓
	Stress	✓	✓	✓	✓	✓
	Resilience	✓	✓	✓	✓	✓
	Coping	✓	✓	✓	✓	✓

^a^HF: heart failure.

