#### Health Care Utilization

Health care utilization is determined by the frequency of emergency department visits and readmissions for HF and assessed via self-report. There are acceptable levels of agreement between self-report and medical record data [30].

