### Expected Outcome

We anticipate that the CARE-HF intervention will improve problem-solving, HF self-care, health-related quality of life, resilience, and coping and decrease HF symptoms, health care utilization, depressive symptoms, anxiety, and stress across all time points from baseline.

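### Table 1 gives health care utilization no baseline measurement, contradicting the abstract and aim 2 and leaving the utilization part of Hypothesis 2b without a reference value; the recall window is also unstated although visit gaps double

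*Protocol article*

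**What the plan says.** All references are to the protocol article.

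- **Purpose, Aims, and Hypotheses.** Hypothesis 2b predicts that decreases in HF symptoms, "health care utilization, depressive symptoms, anxiety, and stress will be seen at 3 months from baseline", and that they will last to 18 months. Aim 2 in the same section lists utilization among the outcomes to be examined at baseline and at all four follow-ups. The Methods part of the abstract does the same.
- **Expected Outcome.** The intervention is expected to "decrease HF symptoms, health care utilization, depressive symptoms, anxiety, and stress across all time points from baseline".
- **Table 1.** The row "Health care utilization" has an empty baseline cell and ticks at 3, 6, 12 and 18 months. Each of the other eight outcome rows has five ticks.
- **Data Collection.** The general rule is "Data are collected at baseline and 3, 6, 12, and 18 months from baseline". The baseline form is described as a "sociodemographic and clinical survey (age, gender, comorbidities, education, and HF class"; prior utilization is not in that list. The section adds "We also collect data on standard Veterans Administration Office of Rural Health metrics" without saying what these contain.
- **Study Measures.** "Health care utilization is determined by the frequency of emergency department visits and readmissions for HF and assessed via self-report". No recall period or denominator is given.
- **Main Analyses.** Every outcome gets the same sequence of multilevel models fitted by REML: intercept only, then linear growth, then quadratic growth. Adjustment for interval length is not mentioned.
- **Follow-Up Telephone Sessions** and **Limitations.** Sessions are weekly in the first month and every two weeks in months two and three, so all eight are over by about month 3. The study has a single group.

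**The concern.** A decrease from baseline needs a baseline value. In a single-group study the pre-intervention measurement is the only reference there is, and for this one outcome Table 1 omits it. Followed literally, the schedule leaves any reported fall in utilization from baseline with no data behind it. This outcome matters to the programme, because the Background reports lower utilization as a notable result of the parent trial.

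The second worry concerns what the four follow-up values mean. A frequency of events depends on how long the veteran was observed. The gap between visits doubles after month 6, and the article gives neither a recall window nor an exposure adjustment. Depending on how the question is asked, the growth curve may describe the visit calendar and not the veterans' use of care.

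**Working it through.** **1. The sections side by side.**

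| Source | Utilization at baseline? |
|---|---|
| Abstract, Methods | Yes, by inclusion in the outcome list |
| Aim 2 | Yes, by inclusion in the outcome list |
| Hypothesis 2b; Expected Outcome | Required by the predicted change |
| Table 1 | No (empty cell, the only such outcome) |
| Baseline survey list | Not listed |
| Rural Health metrics | Content not stated |

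The empty cell is not an extraction fault. The social support row of the same table shows ticks and blanks placed as expected.

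**2. Can the follow-up trend replace the baseline?** Let λ0 be the event rate before the intervention and λ1 the rate after it.

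- If 2b is true, λ1 < λ0, the drop is present by month 3, and the rate then stays at λ1.
- If the intervention does nothing, λ1 = λ0, and the rate stays at λ0.

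From 3 to 18 months both cases predict a flat rate. They differ only in λ1 − λ0, and λ0 is not observed under Table 1.

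**3. Effect of interval length.** The article gives no utilization figure to reproduce, so the rates here are assumptions. Visit times of 3, 6, 12 and 18 months give gaps of 3, 3, 6 and 6 months. If each visit counts events since the last one, the expected count is (rate per year) × (gap in months)/12:

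| Assumed rate per year | Month 3 | Month 6 | Month 12 | Month 18 |
|---|---|---|---|---|
| 0.25 | 0.0625 | 0.0625 | 0.125 | 0.125 |
| 0.5 | 0.125 | 0.125 | 0.25 | 0.25 |
| 1.0 | 0.25 | 0.25 | 0.5 | 0.5 |

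The ratio is 1:1:2:2 at any constant rate.

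For the least-squares slope on time, the mean visit time is 9.75 months and the deviations are −6.75, −3.75, 2.25 and 8.25, with sum of squares 132.75. At 1 event per year the cross-product is 0.25 × (−10.5) + 0.5 × 10.5 = 2.625. The slope is 2.625/132.75 = 0.0198 events per visit per month, although the true rate does not change.

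If the true rate falls by a fraction c after month 6, the ratio of 6-month to 3-month counts is 2(1 − c). That is 1.5 for c = 0.25 and 1.0 for c = 0.5. The rate must halve before the counts stop rising.

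**4. How often this would reach significance.** The simulation used gamma-Poisson counts with dispersion 1, a constant rate, complete data, 4,000 repetitions and n = 80 (100 less 20% attrition). The mean within-person linear slope was tested at |z| > 1.96, as a stand-in for the planned model. Share of trials with a significant increase:

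| Assumed rate per year | Since last visit, unadjusted | Divided by interval length | Fixed 3-month recall |
|---|---|---|---|
| 0.25 | 37% | 3.7% | 2.1% |
| 0.5 | 62% | 3.6% | 2.3% |
| 1.0 | 91% | 2.6% | 2.2% |

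With n = 100 the unadjusted figures are 44%, 73% and 96%. The nominal upper-tail rate is 2.5%, so either remedy largely or wholly removes the artefact. A fixed 3-month recall has its own cost: months 6–9 and 12–15 are never asked about. Neither remedy supplies the missing baseline.

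**The case against.** Several parts of the other side stand.

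- **Baseline status.** A reader might infer from Table 1 that utilization is definitely not collected at baseline. The abstract and aim 2 say otherwise, and the unlisted Rural Health metrics could hold it. What the documents support is a contradiction to be reconciled.
- **Scope.** A reader might take Hypothesis 2b as a whole to be untestable. It names five outcomes, and the other four have baseline ticks. The utilization trend from 3 to 18 months can also still be estimated; it just does not answer 2b.
- **Interval length.** It is tempting to say that a constant rate will look like an increase. That holds only with counting since the last contact and no adjustment for exposure, and the article states neither. Such detail may sit in a fuller protocol or analysis plan. The simulation also tests a linear slope, whereas the article compares three models by AIC and BIC.
- **Hidden benefit.** One might add that unequal windows would mask a real decline over follow-up. But 2b predicts an early drop that is then held, not a continuing decline, so a simulated decline does not represent it.
- **Readmissions.** The term might be read as excluding first HF admissions, since prior admission is not an entry criterion. The definition does not say so; it is only unclear.

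It is also fair that utilization is one of nine outcomes, that the Limitations section admits the lack of a comparison group, and that a later randomized trial is foreseen. This limits the damage but does not supply a baseline value.

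**Conclusion.** The point holds in two parts of different strength.

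The first rests on the text alone. Table 1 conflicts with the abstract and aim 2, and if Table 1 is followed, the predicted fall in utilization from baseline cannot be estimated. With one group and an intervention finished by month 3, follow-up data alone cannot separate an early sustained drop from no effect. This concerns one of the five outcomes in 2b and the matching part of Expected Outcome.

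The second is conditional. If events are counted since the last contact and analysed without regard to interval length, a constant rate doubles the expected count at 12 and 18 months. A false significant increase then appears in roughly 37% to 91% of trials at 0.25 to 1 event per year with 80 veterans. The rates, the dispersion and the simplified slope test are assumptions. Under a fixed recall window or a per-month rate the problem disappears.

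**What to change.** 1. **Reconcile** Table 1 with the abstract, aim 2, Hypothesis 2b and Expected Outcome. If baseline utilization is collected, correct the table and state the look-back period.
2. **If it is not collected**, choose one of two routes. (a) Add a fixed look-back question on emergency department visits and HF admissions to the baseline call for new enrollees. (b) Take utilization out of the from-baseline hypothesis and describe it as an event rate over follow-up.
3. **State the recall window** for every visit. Analyse utilization with a Poisson or negative binomial mixed model with a log person-time offset.
4. **Clarify** whether readmissions includes first HF admissions.

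The cost is one or two extra questions, a separate model for one outcome and, under route (b), a weaker claim for utilization. Route (a) is only a partial cure. At the December 2024 count 56 veterans were enrolled, so at most 100 − 56 = 44 could give a look-back at their own baseline. Of the 56, 4 had completed and have no next call. The other 52 could only be asked retrospectively, some long after enrolment and after the intervention; such answers are weaker and should be flagged. A look-back restores the before-after contrast but does not replace a comparison group.
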